### Validity and reliability of measurement instruments

The validity of the socio-demographic characteristics questionnaire and the obstetrics history questionnaire will be assessed through content and face validity. The literature review shows that the psychometric properties of all the measurement instruments of this study including Childbirth Experiences Questionnaire version 2.0 (CEQ 2.0) (40), Delivery Fear Scale (DFS) (41), PSS_I (PTSD Symptom Scale 1) (35), Edinburgh's Postpartum Depression Scale (42) except PCQ, have been evaluated and confirmed in Iran.

The literature review showed that the psychometric properties of the PCQ have not been assessed in Iran. To evaluate the psychometric properties of the PCQ, the necessary written permission will first be obtained from the developer of this measurement instrument. Its validity will then be assessed using translation validity (forward and backward translation) as well as content validity, face validity, and construct validity. For translation validity, the items will be first translated semantically from English to Farsi by at least two translators fluent in Farsi and English. The translated version will then be reviewed by another translator. The next step will be to translate the reviewed version from Farsi to English by one to three translators fluent in both languages who were not involved in the translation of the original version to Farsi. The final version will be then revised by three to four translators (a language specialist, an expert in questionnaire translation, a specialist familiar with concepts, and a coordinator) (43).

Face validity of the PCQ will be assessed by using a qualitative method (examining the items to identify possible ambiguities, inadequacy, and difficulties in understanding and also to ensure the appropriate fit and relevance of the items) and a quantitative method called impact score (impact scores greater than 1.5 are considered acceptable).

Moreover, a qualitative method (checking the grammar, vocabulary, importance, and placement of items in the appropriate places and also the time required for completing the questionnaire) and a quantitative method (calculating the CVR [Content Validity Ratio] and the CVI [Content Validity Index]) will be employed for evaluating the content validity of this questionnaire.

Construct validity will be examined by exploratory factor analysis (EFA) and confirmatory factor analysis (CFA). Moreover, the test-retest method will be used to assess the reliability of this tool in terms of reproducibility (ICC = intra-class correlation) and internal consistency (Cronbach's alpha). The data needed for the evaluation of research instruments will be collected 4–6 weeks after delivery.

Considering the 25 items of the PCQ, the minimum sample size for validation should be 125. Nevertheless, since the cluster sampling method will be used in this study, and considering a design effect equal to 2, the final sample size will be equal to 250 postpartum women (4–6 weeks after childbirth). After briefing the participants on the research objectives and procedure and getting their written consent, they will be asked to fill out the PCQ.

### Data analysis

The obtained data will be entered into the software using the double data entry approach and will be statistically analyzed in SPSS 24. The socio-demographic and obstetric information will be described using descriptive statistics, i.e., frequency, percentage, and mean (standard deviation) if the data follow a normal distribution pattern or median (the 25th to 75th percentile) if they do not follow a normal distribution pattern. The independent t-test and the chi-square test in the bivariate analysis and the general linear model (after controlling for the socio-demographic and obstetric characteristics) in the multivariate analysis will be also employed to compare the study groups in terms of the childbirth experience, fear of childbirth, postpartum depression, PTSD symptoms, duration of childbirth procedure, Apgar score (one and five minutes after birth), willingness to give birth to another child, and type of delivery. The missing data will be handled by the multiple imputation method). The sensitivity analysis will be done by comparing the results of the modified intention to treat analysis with the imputed data analysis.

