### Sample size

The sample size was calculated in G-Power based on the two primary outcomes of the childbirth experience and fear of childbirth. According to the findings of Shakarami et al. (26) regarding the fear of childbirth and assuming *M*_1 _= 69.3, *M*_2 _= 58.9 (considering a 15% clinically significant increase caused by the intervention based on expertise panel), SD_1 _= SD_2 _= 8.5, two-sided *α* = 0.05, and test power = 95%, the calculated sample size (*n*) was 19. Moreover, according to the findings of Ghanbari et al. (27) about childbirth experience and assuming *M*_1 _= 2.71, *M*_2 _= 3.25 (considering a 20% clinically significant increase caused by the intervention based on expertise panel), SD_1_ = SD_2_ = 0.73, two-sided *α* = 0.05, and test power = 95%, the sample size (*n*) increased to 49. Finally, assuming an attrition rate of 10%, the final sample size (*n*) in each group will be 54. This sample size has the power of 99% to test between-group differences in terms of fear of childbirth.

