### Outcomes

Primary outcomes included birth experience, fear of childbirth, and mother's satisfaction with the quality of intrapartum care.

Secondary outcomes included postpartum depression, post-traumatic stress disorder, desire for giving birth to another child, normal vaginal childbirth, Apgar score, exclusive breastfeeding, duration of the first stage of labor, duration of the second stage of labor, duration of the third stage of labor, and face, content, and construct validity and also the reliability of the Pregnancy and Childbirth Questionnaire (PCQ).

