### Data collection tools

A socio-demographic characteristics questionnaire: This questionnaire will consist of questions about the participant's age, spouse's age, age at marriage, educational attainment, job status, religion, ethnicity, marital status, housing status, household income, place of residence (rural or urban areas), weight before pregnancy, smoking, alcohol, and drug abuse before and during pregnancy.

Obstetrics history questionnaire: This questionnaire contains questions about gestational age, number of pregnancies, number of abortions, attendance at pregnancy classes, pregnancy status (wanted or unwanted), type of previous delivery (if there have been previous pregnancies), and history of pregnancy complications.

Childbirth Experience Questionnaire (CEQ2.0): This 25-item questionnaire measures four main domains of women's childbirth experience: own capacity (sense of control, personal feeling about childbirth, and labor pain), professional support (obstetric information and care), perceived safety (a sense of security and childbirth memories), and participation (a woman's ability to control her postures and movements and relieve pain during labor and delivery). Twenty-two of the 25 items in this questionnaire are scored using a 4-point Likert Scale (1: I agree, 2: I often agree, 3: I often disagree, and 4: I disagree) and the remaining 3 items are scored based on a Visual Analogue Scale (VAS) (1, 2, 3, or 4 points are given to scores 0–40, 41–60, 61–80, and 81–100, respectively). The validity and reliability of the CEQ 2.0 have been proven in a population of American women. The items with negative concepts (experiencing severe pain, fatigue, fear, and having a bad memory) receive negative scores. Higher mean scores on this questionnaire indicate a more positive childbirth experience (33).

Delivery Fear Scale (DFS): This scale was developed by Wijma to measure women's fear of childbirth during labor (34). It is a valid self-assessment questionnaire that measures fear of childbirth during labor through scores ranging from 1 (totally disagree) to 10 (totally agree). Higher scores indicate higher levels of childbirth fear (35).

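### Two of the three primary outcomes are each tested both unadjusted and adjusted, and the plan does not say which test decides

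*Protocol article*

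**What the plan says.** The Data analysis section of the protocol article names two families of test in one sentence: "The independent t-test and the chi-square test in the bivariate analysis and the general linear model (after controlling for the socio-demographic and obstetric characteristics". The first is labelled bivariate and the second multivariate. Both serve the same purpose, to "compare the study groups in terms of the childbirth experience, fear of childbirth, postpartum depression, PTSD symptoms, duration of childbirth procedure, Apgar score", and the list goes on to willingness to have another child and type of delivery. Neither family is called primary, supportive or sensitivity. The only sensitivity analysis named sets modified intention to treat against imputed data, which concerns missing values.

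The Outcomes section gives three primaries: "Primary outcomes included birth experience, fear of childbirth, and mother's satisfaction with the quality of intrapartum care". The first two are in the analysis list. The third is not, and neither is the secondary outcome exclusive breastfeeding, although the Outcomes section includes it ("normal vaginal childbirth, Apgar score, exclusive breastfeeding, duration of the first stage of labor").

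The Sample size section uses a two-group comparison of means without covariates. For childbirth experience it gives "two-sided *α* = 0.05, and test power = 95%, the sample size (*n*) increased to 49". It does not say that the unadjusted test therefore decides.

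**The concern.** A t-test and a covariate-adjusted linear model on the same score both ask whether the groups differ. Each holds its own 5% level. A plan that runs both and ranks neither does not hold 5% for the pair, because for a borderline result the two p-values can fall on opposite sides of 0.05 and the text gives no rule for which one is reported as the finding. At stake is whether a reader of the results can tell that the conclusion on childbirth experience or fear of childbirth was not chosen after both analyses had been seen. This is separate from having three primary outcomes. It would remain with only one.

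**Working it through.** **1. The plan's own sample size.** Inputs from the Sample size section: two-sided alpha 0.05, power 95%.
- Fear of childbirth: d = (69.3 − 58.9)/8.5 = 10.4/8.5 = 1.22. The two-sample t solution is n = 18.4, so 19 per group, as stated.
- Childbirth experience: d = (3.25 − 2.71)/0.73 = 0.54/0.73 = 0.74. The solution is n = 48.5, so 49 per group, as stated.

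Both figures reproduce. The stated error rate therefore belongs to one unadjusted test per outcome.

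**2. How many covariates could enter.** The article names the whole class of socio-demographic and obstetric characteristics and fixes no subset. Under Data collection tools, the socio-demographic questionnaire has about 15 items ("This questionnaire will consist of questions about the participant's age, spouse's age, age at marriage, educational attainment, job status, religion, ethnicity, marital status" and more) and the obstetric one about 7 ("gestational age, number of pregnancies, number of abortions, attendance at pregnancy classes, pregnancy status (wanted or unwanted" and more). That is 15 + 7 = 22 candidates.

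**3. Chance that at least one test is significant when there is no effect.** Simulation: 49 per group, normal outcome and covariates, a t-test and an adjusted linear model on the same data, 20,000 trials per setting. Each test alone rejects in about 5%. At least one rejects in:

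| Covariates | R² = 0 | R² = 0.2 | R² = 0.4 |
|---|---|---|---|
| 5 | 5.5% | 6.8% | 8.2% |
| 10 | 6.6% | 7.4% | 8.2% |
| 15 | 6.8% | 7.8% | 8.1% |
| 22 | 7.5% | 7.9% | 8.1% |

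Separate runs put the 22-covariate row at 7.0%, 8.0% and 8.4%. Across all settings and runs used for this conclusion the range is about 5.3% to 8.7%. The ceiling for two independent tests is 1 − 0.95² = 9.75%. The results lie below it because both tests use the same data.

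**4. How often the two tests disagree on significance.**
- At the planned childbirth-experience effect (0.74 SD), R² 0 to 0.4: 2% to 4% with 5 covariates and 5% to 8% with 22, so about 2% to 8% overall.
- At an assumed 0.4 SD with 22 covariates: 18% to 28%.

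**5. What adjustment does to power.** With 49 per group the unadjusted noncentrality is 0.74/√(2/49) = 3.66, which gives power of about 95%. Adding k covariates of no prognostic value multiplies it by about √(1 − k/97), where 97 = 98 − 1.
- k = 22: 3.66 × √(75/97) = 3.22, power about 89%.
- k = 2: 3.66 × √(95/97) = 3.62, power still about 95%.

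With 22 covariates, power recovers to 94% at R² = 0.2 and 98% at R² = 0.4. The fix must therefore limit the covariates.

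**The case against.** Reporting unadjusted and adjusted results side by side is ordinary practice. The document is a journal article, and a full protocol or SAP that is not shown might name the deciding analysis. The text nowhere says that the smaller p-value may be picked, so the inflation in step 3 is a worst case. All of this is fair, and it limits the size of the point. It does not remove it, because the article does not leave the comparison to another document. It states the comparison, and states it as two tests of equal standing.

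Three stronger readings are tempting, and the documents do not support them.
- A reader might infer that every outcome, and each primary, has two answers. The analysis sentence omits satisfaction with the quality of care and exclusive breastfeeding. For these the article names no comparison at all, which is a different gap.
- A reader might infer that two tests double the error, or raise it by at least half. The tests are strongly correlated. With 5 covariates and R² = 0 the rate is 5.5%, about 1.1 times the stated level.
- A reader might take 18% to 28% disagreement as the expected rate. It rests on 0.4 SD, an effect that the article does not contain and that lies near 50% power, where disagreement is close to its greatest. The Sample size section plans for 0.74 and 1.22 SD.

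It is also true that naming the t-test as decisive would remove the ambiguity, and that it matches the sample-size calculation. The adjusted model is preferred here because randomization is stratified and a baseline fear score exists.

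**Conclusion.** The point holds for the outcomes in the analysis sentence, including two of the three primaries. For each of them the plan prescribes an unadjusted and an adjusted comparison and ranks neither. If either may be called the result, the false-positive rate per outcome is about 5.3% to 8.7% against the stated 5%. Contradictory verdicts would arise in about 2% to 8% of trials at the planned childbirth-experience effect, and more often if the true effect is smaller. These figures assume 49 analysed women per group and normally distributed outcomes and covariates. The number of covariates and their R-squared are also assumed. The inflation is real but modest. The sample size itself is sound and is not affected. The correction should be made before any outcome data are analysed.

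**What to change.** State in the Data analysis section that, for each primary outcome, one analysis decides: the general linear model with a small covariate set fixed in advance. That set is the parity factor used to stratify randomization (first or second childbirth) and, for fear of childbirth, the DFS score already collected before the active phase. This model gives the single estimate, 95% confidence interval and two-sided 0.05 test. Label the t-test and chi-square results as unadjusted and supportive, unable to establish or overturn the conclusion.

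The cost is a sentence or two of text, and the sponsor gives up the option of relying on the unadjusted p-value. Data collection does not change, and with one or two covariates neither does the sample size.

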#### Study settings

This study will be conducted in two public and also, specialized obstetrics and gynecology hospitals in Tabriz City, Iran (Alzahra and Taleghani). The necessary arrangements were made with the officials of the hospitals and the availability of the required equipment will be ensured before the beginning of the project. In case of any problem during the execution of the study, it will be reported. Alzahra Hospital is a Medical Education and Research Center and also, is one of the gynecological and obstetric referral centers in the northwestern region of the country. This center has 10 labor and delivery rooms (LDR). Taleghani Hospital is another Medical Education and Research Center in Tabriz and generally, mothers with low-risk conditions are admitted there. This center has eight LDRs. Each LDR in these centers is equipped with mother and neonate resuscitation facilities, fetal heart rate monitoring, a warmer, a suction device, a bathroom, and a birth ball. Also, pharmacological pain relief methods are performed at the request of mothers.

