### Randomization and allocation concealment

The participants will be assigned to the study groups by stratified block randomization method (first or second childbirth of woman) in blocks of 4 and 6 and with a 1:1 allocation ratio. For allocation concealment, the intervention name will be written on pieces of paper and put in a series of numbered sealed opaque envelopes. The envelopes will be kept by the head of the maternity ward. After entering the qualified woman and obtaining the informed consent, her name and medical file number will be written on the envelope by the researcher and it will be opened by the head of the ward. After determining the type of intervention, the envelope will be returned to the head of the ward.

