
### Routine care

Routine care in the study settings often includes medical procedures ordered by residents of gynecology. Midwives often take care of several women and opportunities for providing midwifery-led care are very limited. Despite a clear definition of the components of respectful care, not all women receive this model of care, and other components of the intrapartum care model are not prioritized as much as medical and clinical care.

The obstetric information of the participants (e.g., duration of the active phase of labor, duration of the second and third phases of labor, Apgar score, etc.) will be also recorded during and immediately after labor. Moreover, Wijma's delivery fear scale (DFS) will be filled out for the participants before the active phase of labor and then at 7–8 cm of cervical dilation. The participants of both groups will be followed up for 6 weeks after labor and then they will be invited to a relatively quiet place to complete the Childbirth Experience Questionnaire (CEQ 2.0), the Edinburgh Postpartum Depression Scale (EPDS), the Post-Traumatic Stress Disorder (PTSD) Symptom Scale (PSS-I), the Pregnancy and Childbirth Questionnaire (PCQ), and a checklist on willingness to give birth to another child. If answering all the postpartum questions is out of the mother's patience, the interview will be conducted on two separate dates determined by the mother.

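### The fear-of-childbirth analysis leaves out the baseline fear score the trial already collects, and the adjusted model names a broad covariate class instead of the randomisation stratum

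*Protocol article*

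**What the plan says.** The Data analysis section sets out two comparisons: the t-test or chi-square test, and then "the general linear model (after controlling for the socio-demographic and obstetric characteristics) in the multivariate analysis". It applies both to childbirth experience and fear of childbirth, among other outcomes.

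The adjustment class is defined by two questionnaires under Data collection tools. The first runs through "participant's age, spouse's age, age at marriage, educational attainment, job status, religion, ethnicity, marital status, housing status, household income, place of residence" and on to weight, smoking, alcohol and drug abuse. The second covers "gestational age, number of pregnancies, number of abortions, attendance at pregnancy classes, pregnancy status (wanted or unwanted), type of previous delivery" and history of complications.

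The DFS is a separate instrument. According to the Routine care section it "will be filled out for the participants before the active phase of labor and then at 7–8 cm of cervical dilation". Fear is one of the three primary outcomes.

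Allocation uses a "stratified block randomization method (first or second childbirth of woman) in blocks of 4 and 6 and with a 1:1 allocation ratio". Women come from two hospitals. Of one of them, Study settings says that "generally, mothers with low-risk conditions are admitted there"; the other is described as a regional referral centre. Hospital is neither a stratum nor an item on either questionnaire.

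**The concern.** When an outcome is measured at baseline and again at follow-up, the baseline score is usually its best single predictor. Here that score is collected, but the t-test cannot use it and the covariate class named for the model does not contain it. The model spends its degrees of freedom on a long descriptive list instead.

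The randomisation was stratified by first or second birth, and the analysis should carry that factor explicitly. The t-test ignores it, and the model reaches it only through neighbouring variables.

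Two things are at stake: the width of the interval for fear, and, if the long list predicts little, the power for childbirth experience, which is the outcome that set the sample size.

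**Working it through.** **Inputs from the protocol.** Fear: means 69.3 and 58.9, SD 8.5. Childbirth experience: means 2.71 and 3.25, SD 0.73. Two-sided alpha 0.05, power 95%, attrition 10%, 54 per group (all from Sample size). Two totals are used: N = 98 (49 per group, after attrition) and N = 108 (everyone, as with imputed data).

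**Assumed, because the protocol gives neither.** The correlation r between baseline and follow-up DFS (0.3, 0.5, 0.7), and the share of outcome variance R² that the covariates explain.

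**Reproducing the plan's figures.**
- Fear: 10.4/8.5 = 1.224. The noncentral-t calculation gives 18.38, so 19 per group, as stated.
- Childbirth experience: 0.54/0.73 = 0.740. This gives 48.48, so 49 per group, as stated.
- Attrition: 49 × 1.1 = 53.9, so 54, as stated.
- Power for fear at 49 to 54 per group is above 99.9%, consistent with the stated 99%.

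The 49 is therefore the size for an unadjusted two-group comparison.

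**Size of the covariate class.** The socio-demographic questionnaire has 15 items: age, spouse's age, age at marriage, education, job, religion, ethnicity, marital status, housing, income, residence, weight, smoking, alcohol and drug abuse. The obstetric questionnaire has 7: gestational age, pregnancies, abortions, classes, wanted or unwanted pregnancy, type of previous delivery and complication history. 15 + 7 = 22.

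**Formula.** With k randomly distributed covariates, the standard error of the group difference relative to the unadjusted one is √[(1 − R²) × (N − 3)/(N − 3 − k)], on N − 2 − k residual degrees of freedom.

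**Baseline DFS alone (k = 1, R² = r², N = 98).** (N − 3)/(N − 3 − k) = 95/94 = 1.0106.
- r = 0.3: √(0.91 × 1.0106) = 0.959, so 4% narrower.
- r = 0.5: √(0.75 × 1.0106) = 0.871, so 13% narrower.
- r = 0.7: √(0.51 × 1.0106) = 0.718, so 28% narrower.

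**All 22 items, one degree of freedom each, no prognostic value (R² = 0).**
- N = 98: variance × 95/73 = 1.301, standard error × 1.141. Power for childbirth experience falls from 95.2% to 88.6%. A 4,000-run simulation also gave 88.6%.
- N = 108: variance × 105/83 = 1.265, standard error × 1.125. Power falls from 96.8% to 92.2%.
- Power for fear stays above 99% in both cases.

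**Break-even.** The 22 items pay for themselves when R² = k/(N − 3): 22/95 = 23% at N = 98 and 22/105 = 21% at N = 108.

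**Baseline DFS added to 22 uninformative items (k = 23, N = 98, r = 0.5).** √(0.75 × 95/72) = 0.995. The gain from the baseline score is almost entirely used up.

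**Cost of a short model for childbirth experience (N = 98).** One uninformative covariate, such as the stratum, leaves power at 95.0%; three leave it at 94.6%.

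**Is parity in the model?** Only first or second deliveries are eligible, and vaginal birth after cesarean is excluded. Type of previous delivery can therefore be only none or vaginal, and coded that way it reproduces the stratum. Pregnancies and abortions add to the same information. The stratum is thus mostly present, but it is not named as such.

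**The case against.** **Covariate lists belong in the analysis plan.** The exact list, its coding and the choice of primary analysis are often settled there, and their absence from an article is not a fault. That stands. It does not answer the baseline point, because the article states a covariate class and the DFS lies outside it.

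**The gain for fear changes no conclusion on power.** This is true: power for fear exceeds 99% with or without adjustment, and randomisation keeps the unadjusted comparison unbiased. What remains is a narrower interval on a primary outcome at no data cost.

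**Stronger readings that the document does not support.**
- A reader might infer that parity is omitted. It is not; the obstetric items carry most of it. The fair criticism is that the randomisation factor is not entered explicitly.
- A reader might infer that the model loses precision. That is conditional: all 22 items must enter, which the text does not say, and together they must explain less than about 21–23% of the variance. The document gives no figure either way.
- A reader might infer that leaving out hospital is an error. Hospital was not a stratum, so the design does not require it. The case-mix remark concerns admissions in general, while the exclusion criteria remove many higher-risk women at both sites. Any figure for chance imbalance between hospitals would need a recruitment split that the document does not give.

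**Conclusion.** The point holds in a limited form. The firm part is that baseline DFS is collected and fear is a primary outcome, yet neither stated analysis uses the score. Using it would narrow the standard error for fear by about 4–28% over assumed correlations of 0.3 to 0.7. The benefit is precision, not power.

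The secondary part is that the stratum should be entered by name instead of through proxies.

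The conditional part is the breadth of the covariate class. At worst, with 22 uninformative single-degree-of-freedom items, power for childbirth experience falls by about 7 percentage points at 98 analysed (95.2% to 88.6%) and about 5 at 108 (96.8% to 92.2%). If the items explain more than about 21–23% of the variance, the set helps. Nothing here suggests bias or an underpowered fear comparison.

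**What to change.** For each continuous outcome, name as primary one linear model with group and parity stratum (first or second birth). For fear, add baseline DFS. Hospital is already known and may be added as a covariate. Move the wider socio-demographic and obstetric set to a single labelled sensitivity analysis.

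State that the first DFS is completed before the envelope is opened, so that it is a true baseline. Sampling places randomisation at the start of the active phase and Routine care places the first DFS before that phase, which fits. The Abstract mentions randomisation first and does not settle the order.

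The cost is a few lines of analysis wording; all the variables are already collected or known. The small downside is losing whatever precision the wider set would have given. Separate envelope series by hospital are optional.
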